## Abstract

**Background:**

Research on intermittent fasting has shown that it can improve a variety of health outcomes, including blood sugar control, blood lipid levels and blood pressure. Only few studies document longer periods of fasting, especially in rehabilitation participants. Cardiac inpatient rehabilitation follows a multidisciplinary approach including change of health behaviour to reduce patients’ risk of future cardiovascular events. To date, evidence suggests that intermittent fasting can be an effective way to improve health and well-being, but more research is needed to fully understand its long-term effects and factors that promote the implementation. Therefore, the aim of the ongoing InterVFast trial is to investigate the effectiveness of intermittent fasting amongst cardiac rehabilitation patients after 4-week inpatient rehabilitation as well as 3 and 12 months subsequently including patients’ perspective.

**Methods:**

This single-centre randomized controlled trial evaluates the effectiveness of the InterVFast intervention in weight loss (primary outcome). We also examine patients’ acceptance and the effect on relevant outcomes as blood glucose and triglyceride levels, cholesterol and high-sensitivity C-reactive protein. Weight, blood samples and clinical data are collected as part of the initial and final examination during inpatient rehabilitation. During inpatient rehabilitation, participants daily note fasting intervals and meals eaten as well as practicability in a fasting diary. In addition, interviews about perceived advantages and disadvantages and acceptance are carried out with the participants in the IG. A standardized follow-up examination (weight, blood samples) will be carried out by the family doctor after 3 and 12 months (t2 and t3).

**Discussion:**

Compared to other weight-loss intervention studies, our study addresses patients with coronary heart disease and includes patients’ acceptance as well as long-term maintenance. It is hypothesized that participation in the InterVfast intervention will improve relevant health outcomes in a sample of cardiac rehabilitation patients and thus constitute a behavioural prevention strategy to reduce the risk of future cardiac events and improve overall health and quality of life.

**Trial registration:**

ClinicalTrials.gov DRKS00023983. Registered on February 17, 2022.

**Supplementary Information:**

The online version contains supplementary material available at 10.1186/s13063-023-07843-7.

## Introduction

### Background and rationale

#### Cardiac rehabilitation

Cardiac rehabilitation is a programme for patients who experienced heart attack, heart surgery or other cardiovascular events [1, 18, 20]. Cardiac inpatient rehabilitation typically combines exercise, education and counselling in a multidisciplinary approach to reduce patients’ risk of future cardiovascular events [12, 18]. The goals of cardiac rehabilitation include improving cardiovascular health, reducing symptoms and helping patients make lifestyle changes that promote participation in working life [6, 18]. Although adherence to lifestyle interventions is challenging in patients with cardiovascular disease, we previously showed that a low-threshold intervention can improve patients’ motivation to continue to practise home based [20].

#### Intermittent fasting

Intermittent fasting (IF) is an eating pattern that involves alternating periods of fasting and eating [2, 5, 15]. For instance, 16:8-intermittent fasting involves fasting for 16 h a day and eating during the remaining 8 h. While a 16:8 intermittent fasting plan does not specify which foods to eat and avoid, it is beneficial to focus on healthful eating and to limit or avoid highly processed foods [21].

The scientific background of intermittent fasting is based on the understanding of how the body processes food and the effects of caloric restriction on health and longevity.

When we eat, the body breaks down the food into glucose, which is used for energy, and insulin, which helps regulate blood sugar levels. During periods of fasting, the body switches from using glucose as its primary source of energy to using stored fat [4, 11]. This metabolic shift has been linked to a range of health benefits, including improved insulin sensitivity, reduced inflammation and increased autophagy, the process by which the body breaks down and recycles damaged cells [4, 7, 11].

Research on intermittent fasting has shown that it can improve a variety of health outcomes in animal-studies. Wan et al. found that intermittent fasting increases lifespan and improves overall health. Mice that fasted every other day had a longer lifespan and were less likely to develop age-related diseases [26].

Human studies indicate that intermittent fasting improves blood sugar control and blood lipid levels and reduces the risk of type 2 diabetes [22, 25]. Some studies also suggest that intermittent fasting helps to promote weight loss and improve cognitive function [22, 24, 25].

Additionally, intermittent fasting has a range of potential health benefits, including reduced inflammation. Participants who follow an intermittent fasting diet are more likely to lose weight and have greater improvements in insulin sensitivity than those who follow a traditional calorie-restricted diet [13, 16]. Nevertheless, Ostendorf et al. emphasize that more research is needed to fully understand the long-term effects of intermittent fasting [16].

### Objectives

To date, evidence suggests that intermittent fasting can be an effective way to improve health and well-being, but more research is needed to fully understand its long-term effects [16, 22]. Only few studies document longer periods of fasting in high-risk person such as rehabilitation patients. Therefore, the aim of the ongoing InterVFast trial is to investigate the effectiveness of intermittent fasting amongst cardiac rehabilitation patients after 4-week inpatient rehabilitation as well as 3 and 12 months subsequently including patients’ perspective.

### Trial design

Our single-centre randomized controlled trial (RCT) evaluates the effectiveness of the InterVFast intervention regarding short-term as well as long-term weight loss (primary outcome). We also examine patients’ acceptance and the effect on relevant outcomes as blood glucose and triglyceride levels, cholesterol and high-sensitivity C-reactive protein.

## Methods: participants, interventions and outcomes

### Study setting

The study is conducted in the centre for cardiovascular rehabilitation in the city of Leichlingen, North Rhine-Westphalia, Germany. While Leichlingen is a more rural town, the catchment area of the centre is the largest metropolitan area of Germany, a population of over 8 million people within a 50-km radius, including big cities like Cologne (population: 1 million) and Duesseldorf (population: 600.000), but also very rural areas.

### Eligibility criteria

The inclusion criteria for this study are the following: male sex and age between 18 and 60 years, a diagnosis of coronary heart disease (CHD) and a body mass index (BMI) between at least 27 kg/m^2^ and 38.9 kg/m^2^.

The study exclusion criteria are as follows: a *NYHA (New York Heart Association Classification)* Functional Class IV, severe obesity (BMI > 39 kg/m^2^), oncological diseases, gastric or duodenal ulcers and insulin dependent diabetes. Patients with an intellectual disability, a current eating disorder or other psychiatric disorders (psychotic disorders, bipolar disorder, substance dependence, or anxiety and depressive disorders) are excluded.

However, we decided to exclude women because of the following reasons: first, some evidence indicates that intermittent fasting may have negative effects on reproduction and blood sugar levels in some women [3, 8, 17]. In all likelihood, such an intervention would produce different results not only in men and women but also in pre- and postmenopausal women [19, 23].

Secondly, female patients are generally underrepresented in cardiac rehabilitation (female-to-male ratio 1:4)^1^ as well as in our study centre. In 2022, only 15% of all patients with CD were female. Therefore, to enroll an adequate number of patients in reasonable time, we solely recruited male patients. Over and beyond, only few studies on lifestyle changing interventions such as intermittent fasting address men. Since men are underrepresented relative to women in current research concerning intermittent fasting, this trial still enriches the existing state of research [9, 10].

### Who will take informed consent?

Two qualified and appropriately trained members of the research team are responsible for obtaining consent. Informed consent involves giving information to the potential participant and clarifying the information. In obtaining and documenting informed consent, the research team complies with good clinical practice (GCP) and with the ethical principles of the Declaration of Helsinki [27].

### Additional consent provisions for collection and use of participant data and biological specimens

No additional consent is provided for collection and use of participant data who withdraw; this study does not involve collecting biological specimens for storage.

### Interventions

#### Explanation for the choice of comparators

The primary outcome of this study is difference in mean weight loss between baseline and end of inpatient rehabilitation after 4 weeks (short-term effectiveness). This outcome has been selected as the primary outcome, because intermittent fasting addresses weight as a main risk factor for cardiovascular disease.

#### Intervention description

The InterVFast intervention was designed by a cooperation of researchers and clinicians from the fields of epidemiology, cardiology and rehabilitation medicine and nutritional advice. The specific contents of the intervention are as follows:

##### 16:8-intermittent fasting

The intervention consists of a 16:8-intermittent fasting programme during the 4-week inpatient rehabilitation. 16:8-intermittent fasting involves fasting for 16 h a day and consuming all calories during the remaining 8 h. For example, a participant starts eating at 11:00 am and stops eating at 7:00 pm. The fasting window is individually adapted to the wishes and needs of the participants.

The fasting programme includes an introduction to the concept of fasting by a nutritionist providing information on the health benefits, practical implementation and fasting tips. Participants in the IG document periods of fasting and meals eaten in a paper-based fasting diary.

A fasting consultation is provided by a trained nutritionist twice a week to answer questions and to track individual progress. Purpose of the consultation can be wants, requests, intentions, preferences or expectations. Besides that, the inpatient rehabilitation programme is carried out as usual.

##### Standard treatment

During 4-week rehabilitation period, the CG receives standard treatment. Regarding eating behaviour, the standard programme includes “healthy-eating” training (2 h), shopping tips for healthy eating (1 h), a teaching kitchen of 3 h, and daily food and beverage buffet training (30 min).

#### Criteria for discontinuing or modifying allocated interventions

Criteria for discontinuing or modifying allocated interventions are any changes in the patient’s condition that justify the discontinuation of treatment in the clinician’s opinion, and participant withdraws consent and confirmation of non-eligibility after registration.

#### Strategies to improve adherence to interventions

During inpatient rehabilitation, a trained nutritionist held regular fasting visits to improve adherence to the fasting programme.

#### Relevant concomitant care permitted or prohibited during the trial

There are no restrictions regarding concomitant care during the trial.

#### Provisions for posttrial care

Participants are able to contact the research team during the study period as well as after the end of participation.

### Outcomes

The primary outcome of this study is difference in weight loss between baseline and end of inpatient rehabilitation after 4 weeks (short-term effectiveness). Secondary outcomes are difference in weight loss between baseline and 3 and 12 months after inpatient rehabilitation (long-term effectiveness), changes in blood pressure, fasting blood glucose and lipids and changes in diet as well as patients’ acceptance.

Weight, blood samples and clinical data are routinely collected as part of the initial and final examination. During inpatient rehabilitation, participants note daily periods of fasting as well as practicability (rating scale from 0 — very bad to 5 — very easy) in a fasting diary. They record all food and drinks, type of meal (breakfast, lunch, dinner, or snack), type of food and portion size. In addition, we carry out interviews about perceived advantages and disadvantages and acceptance with all participants in the IG.

After initial examination at admission (baseline, t0), three follow-up times are provided: final examination at the end of inpatient rehabilitation after 4 weeks (t1), as well as two follow-up times after inpatient rehabilitation after 3 and 12 months. The World Health Organization-Five Well-Being Index (WHO-5) is used for self-reported measure of current mental wellbeing at t0 and t1. A standardized follow-up examination (weight, blood samples) will be carried out by the family doctor at t2 and t3 for valid information. A financial incentive will be paid to family doctors for examination and data transfer.

Sociodemographic characteristics and comorbidities at baseline will be collected as moderating variables. Stable covariables (e.g. sociodemographic characteristics) will be collected only at baseline, while changeable variables will be measured at baseline and follow-up.

#### Participant timeline

Eligibility screening took place at initial admission examination (t0) involving medical history review, physical exams and laboratory tests. Figure 1 shows the schedule of enrolment, intervention and assessments.

**Fig. 1 Fig1:**
[figure not shown]
Schedule of enrolment, intervention and assessments

Patients who met the inclusion criteria were invited to provide study information at the beginning of the inpatient rehabilitation in a personal conversation. We explained the study’s purpose, procedures and potential risks and benefits to the patient. Each patient received appropriate written participant information and an informed consent form.

#### Sample size

A before-and-after comparison between the intervention group (IG) and the control group (CG) will be used for the evaluation. Follow-up values were assessed at t1, t2 and t3. Regarding the primary outcome, the intervention is considered effective if mean difference in weight loss after 4 weeks (t1) in the IG is at least 2% higher than in the CG compared to baseline (t0). The standard deviation of mean difference is estimated at 3.5 kg. The significance level should be 5%. In order to demonstrate difference in weight with a power of 80%, a two-tailed *t*-test requires a total of 100 patients (50 per group).

#### Recruitment

Based on an estimated participation rate of 20%, a period of 6 months was planned for the implementation of the intervention and patient enrollment.

### Assignment of interventions: allocation

#### Sequence generation

As soon as the patient gave written consent, randomization was performed. Randomization took place at individual level, i.e. every single patient was assigned either to the IG or to the CG. A statistician who is not involved in the study generated the randomization list using computer-generated random numbers.

#### Concealment mechanism

The research team member recruiting the patients contacted the randomization office by phone or secure computer after the patient was enrolled in the study (central randomization).

#### Implementation

After eligibility screening took place at initial admission examination (t0) involving medical history review, physical exams and laboratory tests, two trained members of the research team enrolled patients. To minimize the effect of bias, the random allocation sequence remained concealed from those enrolling patients into the study.

#### Assignment of interventions: blinding

Considering the nature of the intervention, participants and therapists cannot be blinded. So, the design of the study is open label; therefore, unblinding will not occur.

The statistician was not blinded, because, to our mind, the statistician should have a good knowledge of the topic of cardiovascular rehabilitation and the intervention. The statistician was not involved in the intervention and data collection.

### Data collection and management

#### Plans for assessment and collection of outcomes

The primary outcome of this study is difference in weight loss between baseline and end of inpatient rehabilitation after 4 weeks.

Secondary outcomes are difference in weight loss between baseline and 3 and 12 months after inpatient rehabilitation, changes in blood pressure, fasting blood glucose and lipids and changes in diet as well as patients’ acceptance.

Weight, blood samples and clinical data are routinely collected as part of the initial and final examination. During inpatient rehabilitation, participants note daily periods of fasting as well as practicability (rating scale from 0 — very bad to 5 — very easy) in a fasting diary. They record all food and drinks, type of meal (breakfast, lunch, dinner, or snack), type of food and portion size.

After initial examination at admission (baseline, t0), three follow-up times are provided: final examination at the end of inpatient rehabilitation after 4 weeks (t1), as well as two follow-up times after inpatient rehabilitation after 3 and 12 months. The World Health Organization-Five Well-Being Index (WHO-5) is used for self-reported measure of current mental wellbeing at t0 and t1. A standardized follow-up examination (weight, blood samples) will be carried out by the family doctor at t2 and t3 for valid information.

#### Plans to promote participant retention and complete follow-up

To assure participant retention and completion of follow-up for t2 und t3, we send a reminder about completing the survey to participants who have not yet participated in the follow-up evaluation. A financial incentive will be paid to family doctors for follow-up examination and data transfer.

All baseline data is collected also for participants who discontinue or deviate from intervention protocols.

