### Statistical methods

#### Statistical methods for primary and secondary outcomes

The statistical evaluation is carried out using the statistical software SPSS (IBM SPSS Statistics, version 29). The confirmatory analysis to measure the effect of the intervention will be carried out as an intention-to-treat analysis, i.e. all participants who are randomized are included in the statistical analysis and analysed according to the group they were originally assigned. Additional analyses will focus on secondary outcomes as well as associations between independent and dependent variables.

Fasting diaries will be analysed using in-house nutrition information. The mean daily caloric intakes will be computed.

The WHO-5 uses a 6-point Likert scale ranging from 0 = “at no time” to 5 = “all of the time”. The sum of these answers is multiplied by 4; scores of 50 or lower suggest that participants might suffer from depression.

Between-group differences at baseline will be tested using analysis of variance (ANOVA). To answer the primary research question, the mean difference in weight loss between the two groups is compared using analysis of variance (ANOVA), a two-tailed *t*-test, or Spearman’s correlation coefficient, respectively. Chi-square tests are used to compare proportions. All continuous outcomes will be modelled using linear regression. We will analyse the effect of fasting while taking into account periods of fasting and calorie intake from the fasting diaries. All statistical tests assume a two-sided significance level of 0.05.

Guided interviews are transcribed and coded by two independent researchers along an open coding scheme using qualitative content analysis by Mayring [14] via the software MAXQDA (VERBI GmbH, Berlin, Germany). Qualitative content analysis aims at classifying qualitative data into categories of similar connotation.

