#### Methods for additional analyses

We will analyse the effect of sociodemographic and clinical variables on the primary outcome as well as the effect of periods of fasting and calorie intake. Additionally, stratified analysis will be performed for those who completed t2 and t3 follow-up. All statistical tests assume a two-sided significance level of 0.05.

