#### Methods in analysis to handle protocol non-adherence and any statistical methods to handle missing data

We use the ITT approach; all randomized patients are included in the analysis, based on the groups to which they were initially randomly assigned. To assess the bias of your data due to non-response, we will perform a non-response bias analysis.

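### The promised intention-to-treat analysis of all randomised patients is not backed by the stated data-collection rule, missing-data answer or tests; the exposure is small at 4 weeks and larger at 3 and 12 months

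*Protocol article*

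**What the plan says.** All references are to the protocol article.

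- **Analysis population.** *Statistical methods for primary and secondary outcomes* makes ITT the confirmatory analysis. The section on non-adherence and missing data repeats that "all randomized patients are included in the analysis, based on the groups to which they were initially randomly assigned".
- **Data after discontinuation.** *Plans to promote participant retention and complete follow-up* states: "All baseline data is collected also for participants who discontinue or deviate from intervention protocols". The same section provides reminders for t2 and t3 and a payment to family doctors.
- **Missing data.** Besides the ITT statement, the section on non-adherence and missing data offers only a non-response bias analysis.
- **Tests.** Mean weight loss is compared by ANOVA, t-test or Spearman correlation, and continuous outcomes are modelled by linear regression.
- **Additional analysis.** *Methods for additional analyses* adds that "stratified analysis will be performed for those who completed t2 and t3 follow-up", at the same two-sided 0.05 level as the other tests.
- **Discontinuing the intervention.** The criteria include a change in the patient's condition and "participant withdraws consent and confirmation of non-eligibility after registration". The consent section provides no additional consent for data from those who withdraw.
- **Where the weights come from.** *Outcomes* and *Plans for assessment and collection of outcomes* take the t1 weight from the routine final inpatient examination, and the t2 and t3 weights from the family doctor.

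**The concern.** ITT needs an outcome, or a stated way of handling a missing one, for everyone randomised. The only data rule for patients who stop or deviate names baseline data. Those are measured at admission, before randomisation, so the rule adds nothing to the outcome analysis. A non-response bias analysis describes who is missing but supplies neither a value nor an estimator that includes them. The ITT label and the stated methods therefore part company as soon as a weight is absent.

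At stake is a bias that could favour fasting. Only the intervention group can stop fasting, and stopping is plausibly linked to smaller weight loss. If such patients are also less often weighed, the observed intervention mean is too favourable. The trial is open label, the statistician is not blinded, and *Trial status* reports t1 as complete. A choice about missing weights that is not fixed in writing could thus be made with allocation and outcomes in view.

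**Working it through.** **1. The plan's own figure.** *Sample size* sets the target as "mean difference in weight loss after 4 weeks (t1) in the IG is at least 2% higher than in the CG" and adds: "The standard deviation of mean difference is estimated at 3.5 kg". With two-sided alpha 0.05 and 80% power, and 2% read as 2 kg (2% of 100 kg, the reading that gives the stated number):

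n per arm = 2 × (1.960 + 0.842)² × 3.5² / 2² = 48.1, so 49. The exact t-test needs 49.05, so 50 per arm and 100 in total.

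The stated total is reproduced. It is a number of evaluable patients, with no allowance for missing weights. The mixing of per cent and kg is a separate matter.

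**2. Does missingness threaten power at t1?** *Trial status* reports 120 consenting patients. Assume that all were randomised, 60 per arm. Up to 1 − 100/120 = 16.7% may then be missing before fewer than 100 remain. T-test power for 2 kg and SD 3.5 kg, with assumed missing rates:

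| Missing | 50 per arm | 60 per arm |
|---|---|---|
| 0% | 80.8% | 87.4% |
| 10% | 76.5% | 83.7% |
| 20% | 71.4% | 79.1% |
| 30% | 65.4% | 73.5% |

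With 120 randomised, power stays near target up to about 20% missing. Bias, and the accuracy of the ITT label, matter more than power here.

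**3. Bias of the available-case difference.** Let d be the share of the intervention group without a weight and g the mean weight loss of its measured patients minus that of its unmeasured patients. With no missing controls:

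ITT mean = (1 − d) × measured mean + d × unmeasured mean, so bias = measured mean − ITT mean = d × g.

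Illustration: measured fasters lose 2 kg more than controls, and unmeasured ones lose the same as controls, so g = 2 kg.

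| d (assumed) | Available-case difference | ITT difference, 2 × (1 − d) | Bias | Bias / ITT difference |
|---|---|---|---|---|
| 10% | 2.0 kg | 1.8 kg | 0.2 kg | 11% |
| 20% | 2.0 kg | 1.6 kg | 0.4 kg | 25% |
| 30% | 2.0 kg | 1.4 kg | 0.6 kg | 43% |

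Other inputs move this freely: 5% × 1 kg = 0.05 kg, and 20% × 3 kg = 0.6 kg. If every patient who stops is still weighed, d = 0 and the bias is zero.

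**4. Where d can exceed zero.**

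- *t1:* patients are inpatients and the discharge weight is routine, with no restriction by arm or adherence. A weight is lost only through early departure, withdrawal or a missed examination.
- *t2 and t3:* the weight depends on a visit to the family doctor after discharge. Reminders and payments reduce loss, but nothing says how a missing weight is handled.

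**The case against.** The strongest reply concerns the primary outcome. A reader might infer from the retention sentence that patients who stop fasting have no outcome. The documents do not support that: a patient who stops but stays in rehabilitation is weighed at the final examination and analysed as randomised. Nor does the sentence say that follow-up ends, and the t2 and t3 reminders go to anyone who has not yet responded, whatever their adherence. This stands, and it is why the exposure at t1 is small.

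A reader might also take the discontinuation criteria to equate stopping fasting with leaving the study. That section concerns the allocated intervention only and says nothing about ending outcome collection, so this reading falls.

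It can also be said that imputation and sensitivity analyses belong in a statistical analysis plan, that linear regression does not rule out imputation, and that an extra analysis of follow-up completers beside ITT is common. All of this is fair, and the absence of such detail alone would be no finding. But the article does answer the missing-data question, and it gives a rule for discontinuing patients and names its tests. Those statements do not deliver its ITT definition when a weight is missing, so they need reconciling whatever a further document adds.

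Finally, no text ties stopping during the 4 weeks to missing a later doctor visit. That link is plausible but unproven, and the figures in the working are illustrations.

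**Conclusion.** The point holds in limited form. As written, the plan yields an available-case analysis whenever a weight is missing, so its claim to include all randomised patients is not met in that event. The stronger conclusion, that a completer analysis must result, is not supported: non-adherent patients with a weight stay in, and the number of missing weights is not reported.

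The exposure is small for the primary outcome at t1 and larger for the long-term secondary outcomes at t2 and t3. The bias of 0.2 to 0.6 kg rests on three assumptions that the documents do not supply: 10% to 30% of the intervention group unmeasured, control-like weight loss in those patients, and no missing controls. Its actual size is unknown and could be close to zero at t1.

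This is a should-fix, not a must-fix.

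**What to change.** 1. **Retention section.** State that outcome data at t1, t2 and t3 are sought for every randomised patient regardless of fasting adherence, within the limits of consent. As t1 is complete, this means retrieving discharge weights from routine records. For t2 and t3, which were ongoing, it can still act prospectively.
2. **Primary method.** Replace the unadjusted tests on weight change with one mixed model for repeated measures on the t1, t2 and t3 weights, with arm, visit, arm-by-visit interaction and baseline weight. State the missing-at-random assumption. The 4-week arm contrast remains the primary result.
3. **Sensitivity analysis.** Add a delta-adjusted analysis in which unmeasured intervention patients are assumed to have lost less weight, over a stated range. The mixed model alone would not correct the kind of loss illustrated above. With baseline as a covariate it also gains nothing from a patient with no later weight, so report the number of such patients by arm and cover them here.
4. **Additional analysis.** Label the analysis of t2 and t3 completers descriptive, since it conditions on something that happens after randomisation.

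The cost is revised wording and a little more analysis work. The discharge weights are routine, and payment for the family-doctor examinations is already planned.
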